## Methods

### Study Design

This study is a multicenter, 6-year, phase IV, low interventional trial. Enrollment of 150 patients with MS was planned across 9 specialist MS clinics in Australia. The Therapeutic Goods Australia approved a cumulative dose of cladribine (10 mg) tablets as 3.5 mg/kg body weight over 2 years administered as 1 treatment course of 1.75 mg/kg per year. After 3 years, patients with MS in consultation with their health care provider will discuss the option of redosing with cladribine tablets, if clinically indicated (by relapse or new MRI activity), switch to another DMT, or continue without change (without commencement of any DMT). For those who will be continued on cladribine, additional courses will be administered as per the previous dosing of 1.75 mg/kg per year.

### Eligibility Criteria

Patients must meet the criteria as described below (Textbox 1).

Inclusion and exclusion criteria.
**Inclusion criteria**
Participants must be eligible for and already intend to commence cladribine tablets in accordance with the Australian Product Information (PI). Cladribine tablets are indicated for relapsing remitting patients with multiple sclerosis who do not have HIV infection, active chronic infection, are immunocompromised, have severe renal impairment, or are pregnant or breastfeeding.Participants must have the ability to understand the purpose and risks of the study, as outlined in the patient informed consent form and provide signed and informed consent and authorization to use protected health information in accordance with national and local privacy regulations.The participants must meet the McDonald criteria [43] for the diagnosis of relapsing remitting multiple sclerosis.Male or female participants aged 18-70 years.Be able to provide details for or consent to provide access to a stored minimum data set (ie, demographics, date of diagnosis, relapse information, and baseline expanded disability status scale score).Be able and willing to comply with all study procedures, including magnetic resonance imaging scanning, as per the protocol.Must agree to use contraception from baseline until 6 months after the last dose of cladribine tablets, unless they or their partners are infertile or surgically sterile.Participants must be aware of all precautions listed in the PI for Mavenclad, and any subsequent disease-modifying therapy treatment received within this clinical study must be adhered to.
**Exclusion criteria**
Participants must not have a concurrent diagnosis of neurological, psychiatric, or other diseases that, in the opinion of the investigator, could impair the capacity to provide informed consent, interfere with study assessments, or impair the participant’s ability to comply with the study protocol.Any contraindication to magnetic resonance imaging scanning.Participants who have any contraindications listed on the Australian PI or who have any of the listed precautions listed on the Australian PI.The subject is considered by the investigator, for any reason, to be an unsuitable candidate for the trial.

### Assessments

#### NEDA Status

NEDA-3 and NEDA-4 status (absence of clinical relapses, confirmed disability worsening, and new T2 lesions, including brain atrophy [NEDA-4 only]) will be assessed based on the clinical data uploaded into the database (MSBase) [44]. For this study, we will use the NEDA-4 criteria as defined by Kappos [16]. Physical examinations, vital sign assessments, and expanded disability status scale (EDSS) assessments will be performed throughout the study. Concomitant medications and adverse events are assessed at every study visit. On the basis of clinical and MRI parameters, patients with MS will be classified as NEDA-positive (responders) or NEDA-negative (nonresponders).

#### MRI Analysis

3D volumetric sequences will be performed annually in routine clinical practice and before treatment switch. The sequence will be performed on the same 3 tesla MRI scanner with a consistent protocol and without gadolinium administration. The images will be transmitted to the Sydney Neuroimaging Analysis Centre for volumetric analysis.

#### BICAMS Test

Cognition will be measured using BICAMS [30]. This test consists of the oral Symbol Digit Modalities Test (SDMT), the immediate word recall trials of the California Verbal Learning Test-2, and the Brief Visuospatial Memory Test Revised [30]. We chose the BICAMS as a cognitive tool over other available cognitive tests because of its ease of administration over multiple sites and a relatively short time frame in which it can be administered.

#### Serum NfL Chain

Serum NfL (sNfL) will be assessed using the Quanterix Simoa platform. This platform has a specialized immunoassay (NF-light) that allows for the detection of neurological biomarkers at very low levels (pg/mL) with excellent consistency and reproducibility. Given the low levels of sNfL, this was the only assay that could be used for this study at the time of study design.

#### Lymphocyte Subsets

##### Overview

Lymphocyte subset analysis is a composite outcome that combines the results from 2 separate subset panels. Owing to the real-world nature of this study, the surface marker selection was based on the markers available at the local pathology services. The results are shown in Table 1.

**Table 1 table1:** Minimum data set from all sites.

Surface marker			Absolute numbers (IU^a^)		Proportional values		How proportional data is derived

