### Lymphocytes as Biomarkers

Blood-based biomarkers are attractive because of their ease of collection and cost-effectiveness. In addition, they may better reflect or even predict disease activity. Lymphocyte subsets may be good markers of disease stability, as many currently used therapies act by restoring the balance of immune cells in the periphery to a *healthy* state. Therapies affecting the B-cell population have been described as effective treatments for MS [21]. This may be related to the suppression of memory B cells. This theory is supported by the failure of Atacicept and tumor necrosis factor α inhibitors in treating MS, both of which result in disease activation [21]. In both ORACLE-MS and CLARITY, cladribine has been shown to markedly reduce B cells, while having a more modest reduction in T cells and natural killer cells [22,23]. A more recent study of the CLARITY cohort further characterized this reduction and demonstrated that memory B cells were the predominantly affected subtype [24].

These studies investigated lymphocyte subsets over the course of 1-2 years. Therefore, a long-term investigation of lymphocyte subsets in response to cladribine treatment is warranted.

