##### T Cells, B Cells, and Natural Killer Cells Panel

T cells, B cells, and natural killer cells (TBNK) panel will be evaluated at each site using the standardized TBNK cocktail from Becton Dickinson. All sites will use the same antibody cocktail for this panel. All results are presented as absolute numbers and percentages of total lymphocytes. Raw flow cytometry data will be obtained from all sites, and concordance measures will be performed to ensure that the reporting of total cells and subsets of cells is consistent between the sites.

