##### B Memory Panel

The second panel will evaluate the B memory cell compartment using antibodies raised against CD45, CD19, CD27, immunoglobulin D, immunoglobulin M, CD21, CD24, and CD38 surface antigens. The minimum panel is gated on the lymphocyte population and assesses CD19, CD27, immunoglobulin D, and CD38. Table 1 lists the minimal data set for each site.

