#### Association Modeling

Our primary outcome is treatment response status according to NEDA 3. We will perform parametric statistical analysis to determine whether any clinical parameters are associated with outcome—the dependent variable. Multiple repeated measurements of the same individual will be obtained. Therefore, we will apply generalized linear mixed models for binary outcomes, with random effects for time points to account for within-subject correlations and clustering. Clinical factors included in the primary analysis will be EDSS, MRI, and relapse rate measures regressed at baseline. Confounding factors (age, sex, disease duration, etc) will be included as required. By carefully defining covariate values in terms of lagged or leading indicators of study factors, longitudinal data will help us to establish the direction of causation and any lags involved. We will also use Mendelian randomization techniques to help dissect causation from the correlation of evidence for causality. In this analysis, all predictor biomarker variables will be modeled individually and yield a test-specific (unadjusted) *P* value. However, we will apply a Benjamini-Hochberg false discovery rate to adjust the raw *P* value for multiple testing while maintaining power. The secondary outcome variables will be modeled similarly using mixed models with specific parameters dependent on the type of data.

To identify multi-biomarker signatures that predict response in this patient cohort, we will also use machine learning algorithms on the patient cohort data set. Specifically, elastic-net regularized generalized linear model analyses using logistic, linear, or multinomial or Poisson models (depending on the outcome variable) will be conducted within a cross-validation routine to avoid overfitting. This will be performed on the entire factor set using the GLMNet package in the R program [46]. Briefly, GLMNet fits a generalized linear model via penalized maximum likelihood and is akin to a stepwise forward regression with the added feature of being able to perform internal cross-validation. GLMNet allows for both binary and multinomial outcomes. GLMNet allows for the rapid discovery of reduced factor panels that are likely to be associated with outcomes. This complementary approach is not susceptible to multiple testing burdens and will facilitate the identification of the best fitting multifactor signature that is predictive of treatment response [46].

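### The between-site safeguards for flow cytometry are written for the TBNK panel and not repeated for the B memory panel, and no site or laboratory term is named in the models

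*Protocol article*

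**What the plan says.** All references are to the protocol article.

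- **Study Design:** "Enrollment of 150 patients with MS was planned across 9 specialist MS clinics in Australia".
- **Lymphocyte Subsets, Overview:** "the surface marker selection was based on the markers available at the local pathology services". Table 1 then sets a minimum data set for every site, with a phenotype and a denominator for each subset. CD27, IgD and CD38 appear in the B memory part only, as proportions.
- **TBNK panel:** "All sites will use the same antibody cocktail for this panel". The same paragraph adds: "Raw flow cytometry data will be obtained from all sites, and concordance measures will be performed", so that totals and subsets are reported consistently across sites.
- **B Memory Panel:** "The second panel will evaluate the B memory cell compartment using antibodies raised against CD45, CD19, CD27" and five further antigens. "The minimum panel is gated on the lymphocyte population and assesses CD19, CD27, immunoglobulin D, and CD38". Nothing is said here about a common reagent, raw files or concordance.
- **Association Modeling:** generalized linear mixed models for binary outcomes, "with random effects for time points to account for within-subject correlations and clustering". The confounder list gives age, sex and disease duration, is left open, and applies as needed. Site and laboratory are not named.
- **End Points:** lymphocyte subsets are additional outcomes, analysed as change over time from baseline.

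**The concern.** The Introduction reports from earlier cladribine data that "memory B cells were the predominantly affected subtype", so the B memory panel carries the leading cellular hypothesis. It is also the panel for which the text states fewer cross-site controls. A shared marker list does not by itself align antibody clones, gates or instruments.

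Local testing implies that each patient's samples go to one clinic's laboratory, so any laboratory offset is nested in site. An effect for time point cannot absorb a shift that is constant within a laboratory and differs between laboratories. If such shifts exist and sites are pooled, they go into the error of the responder contrast. If NEDA rates also differ between clinics, part of the shift is read as a difference between responders and nonresponders.

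**Working it through.** **1. The plan's own figures.** Enrolment: 120 / (1 - 0.20) = 150. Groups: 0.50 x 120 = 60 and 60. Both reproduce. The 80% power for a 10% mean difference at a false discovery rate of 0.05 cannot be reproduced, because the Sample Size Calculation section gives neither a standard deviation (SD) nor a number of tests.

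**2. Implied SD.** For 60 v 60, two-sided 5% (sidedness assumed), normal approximation:

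SD = 10 / [(1.960 + 0.842) x sqrt(2/60)] = 10 / 0.511 = 19.5%, a standardized effect of 0.51.

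At a threshold of 0.005, as a stand-in for multiplicity, the implied SD is 15.0% (effect 0.67).

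**3. Adding laboratory variance.** Assume that this SD excludes laboratory variance, and that laboratories hold a share f of total variance. Then total SD = SD / sqrt(1 - f), and the number per group for 80% power is 60 / (1 - f).

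| f (assumed) | Total SD | Power at 0.05 | Power at 0.005 | Per group for 80% |
|---|---|---|---|---|
| 10% | 20.6% | 76% | 74% | 67 |
| 20% | 21.9% | 71% | 68% | 75 |
| 30% | 23.4% | 65% | 60% | 86 |

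(Total SD and the per-group number are for the 0.05 row of inputs.)

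**4. False positives without a site term.** Simulation with 120 patients, 9 sites of nearly equal size, no true difference, t test, 5000 runs per cell:

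| SD of site responder rate (assumed) | f = 10% | f = 20% | f = 30% |
|---|---|---|---|
| 0 | 4.8% | 5.2% | 4.6% |
| 0.10 | 5.1% | 6.4% | 6.2% |
| 0.20 | 6.9% | 9.0% | 11.5% |

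With fixed site effects every cell lies between 4.2% and 5.3%. Inflation needs both ingredients: laboratory offsets and unequal NEDA rates.

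**5. Random site intercept.** Further simulations used 120 patients in 9 sites, a standardized effect of 0.516 (80% power with no laboratory effect), and site NEDA log-odds with SD up to 0.8. At f = 20-30%, power is about 63-72% without a site term and about 72-77% with a random intercept. When site odds vary, false positives are about 7-11% without it and 5-6% with it. With no laboratory effect the random intercept costs at most about 1 power point; fixed site effects cost about 2-7.

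These simulations compare marker levels between responders and nonresponders. The article's primary model has NEDA as the dependent variable and tests the same association from the other side. The figures are therefore a guide to scale and not a power calculation for that model.

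**6. Change from baseline.** If a laboratory adds a constant a, then (later + a) - (baseline + a) = later - baseline, and the offset cancels. If it multiplies by k, the change becomes k x (later - baseline), and the difference between laboratories remains.

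**The case against.** Four stronger readings are tempting, and the article does not support them.

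- **That no model contains a site term.** The article only fails to name one. The confounder list is open, clustering is mentioned, and a condensed article may leave the full covariate list to the complete protocol or SAP.
- **That the B memory panel has no concordance check.** The concordance sentence stands under the TBNK heading, but its wording is general. Only the cocktail sentence is expressly limited to that panel.
- **That the B memory panel is uncontrolled.** Table 1 and the B memory section fix a minimum marker set, phenotypes, denominators and a gating population. The remark on local availability covers both panels, and may mean that the common set was chosen so that every site could deliver it.
- **That power is below 80% and false positives exceed nominal.** The loss of power needs laboratory variance that the planners' SD left out, and no SD is given. The excess of false positives also needs NEDA rates that differ by site.

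The change-from-baseline point also stands for a constant additive offset, and proportions remove errors in count calibration. Neither removes differences in how much of a population a gate captures. Nor does differencing help where a baseline level is itself the predictor, and the Objective section asks whether biomarkers predict response. Finally, the primary end point, the proportion with NEDA, does not depend on flow cytometry.

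What remains is the asymmetry between two adjacent sections, and a stated random-effect structure that cannot take up a laboratory offset.

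**Conclusion.** The point holds in a limited form. The safeguards written for the TBNK panel are not repeated for the B memory panel, and the only random effect named is for time points, across 9 clinics. For analyses that use marker levels to predict NEDA, laboratory differences would cost power, and would bias the responder contrast if NEDA rates vary by clinic. Additive offsets largely drop out of the change-from-baseline outcomes; scale differences do not.

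The sizes rest on an assumed laboratory share of 20-30% of marker variance, a single two-sided 5% test rather than the planned false discovery rate, and assumed variation in site NEDA odds. At a 10% share the harm is small: power about 76%, false positives about 5-7%. The primary end point is untouched. The change is worth making because it costs almost nothing and protects the biomarker analyses whichever share proves true.

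**What to change.** 1. **Association Modeling:** name a random intercept for site (testing laboratory) in every model of a locally measured marker. If laboratories agree, this costs at most about 1 power point. Fixed site effects would cost about 2-7 points, so the random intercept is the better choice.
2. **B Memory Panel:** state that the raw-file and concordance rule in the TBNK section also covers this panel, where the files are retained. If the rule was already meant for both panels, one sentence settles it. The cost is file transfer and the concordance work. The article does not say whether B memory raw files are kept. Follow-up runs to 2027, so it is better to ask the sites now.

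Cross-validation folds by whole site, or centring of markers within laboratory, are matters of preference and are not needed to meet this point.

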**TBNK^b^ panel**							
	CD45	✓^c^		✓		As per the FBE^d^	
	CD3	✓		✓		CD45+CD3+ (T cells as a percentage of total lymphocytes)	
	CD4	✓		✓		CD45+CD3+CD4+ (CD4+ [T helper class] as a percentage of T cells)	
	CD8	✓		✓		CD45+CD3+CD8+ (CD8+ [cytotoxic T cells] as a percentage of T cells)	
	CD19	✓		✓		CD45+CD3−CD19+ (B cells as a percentage of total lymphocytes)	
	CD56/16	✓		✓		CD45+CD56+CD16+CD3− (natural killer cells as a percentage of total lymphocytes)	
**B memory panel**							
	CD45	✓		✓		As per the FBE	
	CD19	✓		✓		CD45+CD19+ (B cells as a percentage of total lymphocytes)	
	CD27			✓		CD45+CD19+CD27+ (memory B cells as a percentage of total B cells)	
	Immunoglobulin D			✓		CD45+CD19+CD27+IgD±(class switched or unswitched as a percentage of memory B cells)	
	CD38			✓		CD45+CD19+CD27+CD38+ (proportion of plasmablasts as a percentage of memory B cells)	

^a^IU: International Units.

^b^TBNK: T cells, B cells, and natural killer cells.

^c^Tick marks indicate where the subset will be presented as absolute numbers (column 2) or as proportional values (column 3).

^d^FBE: full blood examination.

##### T Cells, B Cells, and Natural Killer Cells Panel

T cells, B cells, and natural killer cells (TBNK) panel will be evaluated at each site using the standardized TBNK cocktail from Becton Dickinson. All sites will use the same antibody cocktail for this panel. All results are presented as absolute numbers and percentages of total lymphocytes. Raw flow cytometry data will be obtained from all sites, and concordance measures will be performed to ensure that the reporting of total cells and subsets of cells is consistent between the sites.

##### B Memory Panel

The second panel will evaluate the B memory cell compartment using antibodies raised against CD45, CD19, CD27, immunoglobulin D, immunoglobulin M, CD21, CD24, and CD38 surface antigens. The minimum panel is gated on the lymphocyte population and assesses CD19, CD27, immunoglobulin D, and CD38. Table 1 lists the minimal data set for each site.

#### DNA Methylation

Epigenome-wide DNA methylation will be evaluated using DNA extracted from frozen whole blood samples. Genomic DNA will be bisulfite converted and hybridized to Illumina Infinium MethylationEPIC BeadChip arrays at the lead site. Changes in DNA methylation (differentially methylated positions) will be expressed as population medians. Medians will be used to identify changes between responders and nonresponders that meet both the significance cutoff of *P*<.05, and a threshold of >10% change.

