#### End Points and Outcomes

Participants will attend visits or receive phone calls for assessments at baseline (before 1st dose) and months 1 (before 2nd dose), 3, 7, 12 (before 3rd dose), 13 (before 4th dose), 18, 24, 30, 36, 42, 48, 54, 60, 66, and 72 months, and a variable time point (Tv; at exacerbation of disease and/or before change in treatment or redosing). The schedule of the assessments is shown in Multimedia Appendix 1. BICAMS will be performed annually. MRI will be performed yearly, plus one additional scan 6 months after the first treatment course. Lymphocyte subsets (TBNK and B memory panels) will be performed at screening and at 3, 7, 12, 18, 24, 36, 48, 60, 72, and Tv. Serum NfL will be assessed at screening and at 3, 7, 12, 18, 24, 36, 72, and Tv. DNA methylation and RNA collection occur at screening and at 7, 24, 72, and Tv.

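### Methylation positions are selected in unsorted whole blood with no cell-composition adjustment specified, so shifts in cell mix under a lymphocyte-depleting drug can be read as epigenetic change

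*Protocol article*

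**What the plan says.** The DNA Methylation section of the protocol article fixes the tissue ("Epigenome-wide DNA methylation will be evaluated using DNA extracted from frozen whole blood samples") and the selection rule: "Medians will be used to identify changes between responders and nonresponders that meet both the significance cutoff of" P<.05 "and a threshold of >10% change". It mentions no cell sorting, no estimation of cell proportions and no cell covariate, and does not say whether the 10% is in absolute methylation points or relative to a reference group.

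The only sentence on covariates is in Association Modeling: "Confounding factors (age, sex, disease duration, etc) will be included as required". Cell composition is not named.

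Under Lymphocytes as Biomarkers the article reports that "cladribine has been shown to markedly reduce B cells, while having a more modest reduction in T cells and natural killer cells".

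End Points and Outcomes gives the timing: "DNA methylation and RNA collection occur at screening and at 7, 24, 72, and Tv", while the lymphocyte panels "will be performed at screening and at 3, 7, 12, 18, 24, 36, 48, 60, 72, and Tv". The End Points section adds two further methylation comparisons: change from baseline, and Tv against a time point of stable disease.

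**The concern.** A whole-blood methylation value is an average over cell types, weighted by their share of leukocytes. It can move because methylation changed inside cells or because the mix of cells changed. The stated rule cannot tell these apart, and the study drug acts on the mix.

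The planned comparisons are not equally exposed:

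- **Change from baseline** contains the depletion directly.
- **Tv versus stable disease** compares samples that can lie at different stages of depletion and recovery.
- **Responder versus nonresponder** is affected only if composition differs by response. Study Design offers one route: after year 3, patients with relapse or new MRI activity may be redosed or switched, so disease activity influences treatment, and treatment can influence cell mix before the month 72 sample. The article also studies lymphocyte subsets as candidate markers of disease stability.

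At stake is the interpretation of hits. The introduction presents methylation as a potentially specific marker of treatment response. A hit that may reflect cell counts cannot support that claim.

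**Working it through.** **1. The plan's own figures.** Sample Size Calculation: 150 × (1 − 0.20) = 120 evaluable, and 120 × 0.5 = 60 per response group. Both reproduce. The stated 80% power cannot be checked, because neither an SD nor a number of tests is given; nothing below depends on it. The 10% filter has no derivation to reproduce.

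**2. Visits.** Methylation: screening, 7, 24, 72, Tv. Lymphocyte panels: screening, 3, 7, 12, 18, 24, 36, 48, 60, 72, Tv. Every methylation visit has a panel.

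**3. Size of a composition effect.** With two compartments (lymphocytes, other leukocytes) and no change within any cell:

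change in methylation = change in lymphocyte share × methylation difference between compartments (D).

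The article gives no cell shares and no D, so these are assumptions, shown as ranges. The shift in share needed for 10 absolute points is 0.10 / D:

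| D | Shift needed (points) |
|---|---|
| 1.0 | 10.0 |
| 0.9 | 11.1 |
| 0.7 | 14.3 |
| 0.5 | 20.0 |

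For a relative threshold, take methylation of 0.05 + 0.9 × share and an assumed mean share of 18%. The reference value is 0.05 + 0.9 × 0.18 = 0.212. Ten percent of it is 0.0212, and 0.0212 / 0.9 = 0.024, a gap of about 2.4 points.

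**4. Within-patient change.** With non-lymphocytes unchanged, the share after depletion d from a starting share L is L(1 − d) / [L(1 − d) + 1 − L]. For L = 30% and d = 50%: 0.15 / 0.85 = 17.6%, a fall of 12.4 points, which moves methylation by 0.9 × 12.4 = 11.1 points. Over L = 25–35% with D = 0.9:

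| Lymphocyte depletion | Absolute shift (points) | Relative shift |
|---|---|---|
| 30% | 5.5–6.9 | 19–20% |
| 50% | 9.6–12.4 | 34–35% |
| 70% | 14.3–19.0 | 52% |

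B cells alone, assumed to be 2–5% of leukocytes with 90% lost: 0.9 × 0.9 × 0.02 = 1.6 points to 0.9 × 0.9 × 0.05 = 4.1 points. That is below 10 absolute points, but 24–43% relative at a position with low overall methylation.

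**5. Responder versus nonresponder.** Simulation of 60 versus 60, 1,000 runs, no true within-cell difference. Assumed: D = 0.9, share 18% in one group and 18% plus the gap in the other, SD 6 points, methylation noise SD 0.02. Unadjusted: Mann-Whitney P<.05 plus the 10% filter on medians. Share of runs passing both criteria:

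| Gap in lymphocyte share (points) | 10% relative | 10 points absolute |
|---|---|---|
| 0 | 3% | 0% |
| 3 | 63% | 0% |
| 5 | 96% | 0% |
| 8 | 100% | 1.5% |
| 11 | 100% | 45% |
| 13 | 100% | 91% |

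With lymphocyte share as a covariate, P<.05 occurred in 5–6% of runs and both criteria in at most 0.1%, at every gap tested. Two limits apply. The covariate was the true share without measurement error, so this is a best case for adjustment. P<.05 was taken per position, without the false discovery rate step in Association Modeling.

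**The case against.** **Only a condensed article is shown, and its confounder list is open-ended.** This stands in part. A reader might infer that the plan rules out adjustment for cell mix; it does not, and the fair statement is that none is specified. But the article goes beyond leaving a detail open: it fixes tissue, contrast, summary statistic and two cut-offs, and that rule followed as written can give misleading hits.

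**Everyone starts cladribine, so a shared fall in lymphocytes cancels between responders and nonresponders.** This stands. A before/after fall in lymphocyte share does not measure bias in that contrast; only a gap between the groups does. On an absolute reading the gap must be about 11 points or more, and no passage documents one that large. The argument does not protect change from baseline or Tv versus stable disease.

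**Selective B-cell loss is too small to matter.** True for an absolute 10-point threshold under the assumed shares; not true for a relative one.

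**The elastic net uses the entire factor set, so methylation and cell counts can compete in one model.** That is a separate prediction analysis. It does not repair the position-by-position rule.

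**Cell mix may lie on the drug's pathway, and for prediction a signal through it is legitimate.** This stands for prediction, and is why both results should be reported. It does not justify calling such a signal an epigenetic change.

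**Conclusion.** The point holds in a bounded form. The selection rule cannot separate within-cell methylation change from a change in cell mix, no adjustment is specified, and the drug is stated to alter the mix unevenly. The two within-patient comparisons are exposed directly; the responder contrast is exposed conditionally.

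The size depends on a choice the article leaves undefined. In the responder contrast, at a strongly cell-specific position, a gap of 3 to 5 points in lymphocyte share passes a relative filter in 63–96% of simulated runs, yet never passes an absolute one. All cell shares, methylation differences and SDs are assumptions, and nothing here estimates how many positions on the array would be affected.

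Two stronger readings are not supported. A reader might infer that the methylation results would merely restate the lymphocyte counts; the documents show only that the two could not be told apart. A reader might also infer that baseline predictors are contaminated by the drug; the screening sample is taken before the first dose, so cladribine depletion cannot affect it.

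**What to change.** Replace the bare comparison of medians with position-level models that include same-visit cell proportions. These can be estimated from the methylation array itself, or taken from the blood-count differential combined with the TBNK subsets. TBNK alone is not enough, because its percentages are of lymphocytes and not of all leukocytes. If the differential is used, confirm that it is recorded at each methylation visit: in the article the full blood examination appears only as the source of the CD45 rows in Table 1.

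Apply the 10% filter to the adjusted difference and state whether it is absolute or relative. Use the same covariates for change from baseline and for Tv versus stable disease. Report the unadjusted result beside the adjusted one, rest claims of epigenetic change on the adjusted result, and allow the unadjusted one to serve pure prediction.

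The change is to the analysis only and needs no sample beyond those scheduled. It costs a few degrees of freedom, and signal acting through cell mix will appear only in the unadjusted result.
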